### Statistical Analysis

#### Feature Engineering and Selection

For each patient, baseline readings will be based on their first few MouthLab measurements. The number of observations used to establish the baseline will depend on the variability in each patient’s reading. We will then summarize the patient’s parameters obtained from the MouthLab data collection. At each time t, we will include the most recent observations, changes since the last reading, trends, variability in values, and comparison to the patient’s baseline. Additionally, we will include information about demographics, symptom scores, other clinical characteristics, as well as key comorbidities. We anticipate that variable interactions will be important. Given the cohort size and the number of different features, regularization will be applied to avoid overfitting.

#### Outcome Modeling

We will define the outcome as patients experiencing a DE within τ time units (DEτ). For different values of τ, we will deploy a series of more sophisticated models in order to explore the predictive ability of different approaches, as detailed below. We will split up the data into training and testing datasets based on the time of enrollment. We anticipate an 80:20 split; in other words, we will set aside 20% of the data to evaluate the model performance. For each τ, we will construct a training dataset consisting of multiple overlapping time segments for each patient, which we refer to as the observation period (eg, 2 weeks), and multiple nonoverlapping time segments leading up to the outcome for the patients that experience the outcome, one of which contains the outcome.

Second, we will explore several other machine learning algorithms, including classification trees, random forest, and boosting approaches, to understand whether these more flexible modeling approaches have an advantage over the logistic regression approach. The output of any of these approaches is a predicted probability of a DE occurring within the following τ days given observations of a fixed observation interval (eg, up to 30 previous measurements, or ~2 weeks). As stated earlier, the goal is to develop the AIDI to predict worsening health. The detailed analysis laid out above will allow us to understand the ability of early prediction, that is, the critical time frame just prior to decompensation during which the probability of hospitalization becomes increasingly predictive.

The initial exploratory analysis will inform the selection of proper features for the analysis. We will model the patient’s risk of hospitalization as a function of their physiological values, short-term changes in those values, changes from the baseline, etc. The initial exploratory analysis will inform features such as the appropriate time ranges (eg, should short-term changes be captured since the last reading or over the last 24 hours).

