**Objective:**

This study aims to use a single, integrated device—MouthLab, which measures 10 vital health parameters in 60 seconds—and a cloud-based proprietary analytics engine to develop and validate the Aidar Decompensation Index (AIDI), to predict decompensation in health among patients who previously had severe COVID-19.

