**Methods:**

Overall, 200 participants will be enrolled. Inclusion criteria are patients in the US Department of Veterans Affairs health care system; “severe” COVID-19 infection during the acute phase, defined as requiring hospitalization, within 3-6 months before enrollment; aged ≥18 years; and having 1 of 6 prespecified chronic conditions. All participants will be instructed to use the MouthLab device to capture daily physiological data and complete monthly symptom surveys. Structured data collection tables will be developed to extract the clinical characteristics of those who experience decompensation events (DEs). The performance of the AIDI will depend on the magnitude of difference in physiological signals between those experiencing DEs and those who do not, as well as the time until a DE (ie, the closer to the event, the easier the prediction). Information about demographics, symptoms (Medical Research Council Dyspnea Scale and Post-COVID-19 Functional Status Scale), comorbidities, and other clinical characteristics will be tagged and added to the biomarker data. The resultant predicted probability of decompensation will be translated into the AIDI, where there will be a linear relationship between the risk score and the AIDI. To improve prediction accuracy, data may be stratified based on biological sex, race, ethnicity, or underlying clinical characteristics into subgroups to determine if there are differences in performance and detection lead times. Using appropriate algorithmic techniques, the study expects the model to have a sensitivity of >80% and a positive predicted value of >70%.

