One approach to the prevention of decompensation is to monitor for worsening in physiological parameters after hospital discharge. However, collecting such data longitudinally for prediction poses several challenges. First, only a limited number of parameters can be easily collected (eg, blood pressure, heart rate, oxygen saturation, etc), although additional parameters such as heart rate variability and lung function may provide additional prognostic data. Second, even if patients or families are able to collect these parameters longitudinally, there is no automated, validated method to analyze those data concurrently and provide a quantitative assessment of decompensation risk over time. These limitations hinder the sensitivity and thus the utility of current approaches to using physiologic parameters to predict decompensation risk among patients after COVID-19.

The overall objective of this study (trial registration: ClinicalTrials.gov NCT05220306) is to use a handheld, multisensor device—MouthLab, which measures 10 vital health parameters in 60 seconds—and a cloud-based proprietary engine to develop and validate the Aidar Decompensation Prediction Index (AIDI). MouthLab measures oral temperature, single-lead electrocardiogram, heart rate, breathing rate, heart rate variability, respiratory flow morphology, oxygen saturation, pulse rate, and basic lung function (forced expiratory volume in the first second and peak expiratory flow rate). The study will collect MouthLab data from patients previously hospitalized with COVID-19 (“severe COVID-19”) in order to identify decompensation predictor variables. These variables will be used to develop the AIDI to accurately predict decompensation events (DEs) related to post–COVID-19 condition. Index development will follow best practices in machine learning and algorithmic development, where the main outcome is any COVID-19–related event that leads to an emergency department (ED) visit, hospitalization, or the need for escalated care (new diagnosis or change in intervention to manage the chronic conditions). These DE cases will help inform the final set of predictor variables to develop the AIDI. In the future, early prediction and real-time risk triaging using the AIDI may support better clinical decision-making, thus preventing complications, controlling disease progression, and improving outcomes. The aim of this paper is to describe the protocol for this study to develop and validate the AIDI.

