#### Performance Evaluation

In case of a lower-than-expected number of observed outcomes, or smaller differences than expected between those who experience the outcome and those who do not, we may revert from our 80:20 split to use cross-validation to measure performance. In that case, we will evaluate the algorithm using the leave-one-out cross-validation technique. We will implement this approach by leaving out one patient at a time (corresponding to potentially multiple observation periods to avoid fitting the model on data from the same patient as the model is being evaluated). The leave-one-out cross-validation technique facilitates cross-validation evaluation of the algorithm structure to assess its robustness to changes. This validation step will remake the algorithm for every patient left out of the algorithm development iteration. In short, this approach fits each algorithm using all available data except for (in our case) the data of one patient and then summarizes whether the algorithm predicts the correct classification of decompensation or nondecompensation for each observation period. This process is repeated over all available patients. For each τ, we will summarize the accuracy, false positives, and false negatives.

The resulting predicted probabilities of decompensation will then be translated into the easy-to-communicate AIDI, where there is a linear relationship between the risk score and the AIDI. At the conclusion of phase 3, the final COVID-19 DE detection performance of the AIDI will be evaluated using standard measures including sensitivity, specificity, and positive predictive value across a wide range of risk cutoff values. Overall, AIDI DE detection performance and lead time statistics will be examined across study populations as well as within subgroups. If necessary, to improve prediction accuracy, data may be stratified based on biological sex, race, ethnicity, or underlying clinical characteristics into subgroups to determine if there are differences in performance and detection lead times among the groups.

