## Discussion

### Expected Findings

The AIDI study seeks to address a substantial challenge, that is, to develop an affordable, scalable, technology-assisted remote monitoring solution to facilitate early identification of abnormalities and timely intervention by clinicians to improve quality of life, functional status, and health outcomes and, ultimately, to reduce the burden of post–COVID-19 condition in the United States and elsewhere. We hypothesize that monitoring participants for 6 months and capturing critical cardiorespiratory parameters on a daily basis in conjunction with subjective and clinical data will enable the development of an index, the AIDI, that will empower high-quality clinical care using the MouthLab device as a rapid and early assessment tool. The outcomes of this research have the potential to redefine the care delivery for COVID-19 and potentially other conditions in the future, as well as push the boundaries of prevention and care beyond traditional care settings into the home.

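### As described, AIDI performance cannot be attributed to MouthLab, nor the device's added value quantified, because no benchmark model without MouthLab data is planned

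*Protocol article*

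**What the plan says.** All references are to the protocol article.

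- **Aim.** The Abstract (Objective) pairs the MouthLab device with "a cloud-based proprietary analytics engine to develop and validate the Aidar Decompensation Index (AIDI), to predict decompensation in health".
- **Rationale.** The Introduction says that few parameters are easily collected at present, "although additional parameters such as heart rate variability and lung function may provide additional prognostic data", and that such limits reduce the sensitivity of current approaches. The Abstract's Conclusions again put the emphasis on biosensor-derived features.
- **Inputs.** For the MouthLab data, Feature Engineering and Selection says "we will include the most recent observations, changes since the last reading, trends, variability in values, and comparison to the patient’s baseline". It continues: "Additionally, we will include information about demographics, symptom scores, other clinical characteristics, as well as key comorbidities". The Abstract (Methods) agrees: "comorbidities, and other clinical characteristics will be tagged and added to the biomarker data".
- **Comparison.** Outcome Modeling tries classification trees, random forest and boosting "to understand whether these more flexible modeling approaches have an advantage over the logistic regression approach".
- **Evaluation.** Under Performance Evaluation the finished index is "evaluated using standard measures including sensitivity, specificity, and positive predictive value across a wide range of risk cutoff values", with lead-time and subgroup results for the same index.
- **Expected use.** Expected Findings hypothesizes an index that "will empower high-quality clinical care using the MouthLab device as a rapid and early assessment tool".

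**The concern.** Two kinds of predictor enter one model: device signals, and clinical or survey data that could be had without the device. The Introduction itself says that comorbidities raise the risk of complications. The stated comparison changes the algorithm, and nothing in the article says that it changes the inputs. It can show whether boosting beats logistic regression, but not whether MouthLab adds anything to age, comorbidity and dyspnea score.

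What is at stake is how the result is read. A well-performing AIDI may be taken as support for daily use of the device, when the planned figures would look much the same whether MouthLab supplied most of the information or little of it.

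**Working it through.** **1. The plan's own figures.** Sample Size gives 100 DEs, a 60% event rate, 168 completers, 15% dropout and 200 recruited. 100/0.60 = 166.7, so 167 (stated 168). 168/0.85 = 197.6, so 198 (stated 200). 200 × 0.85 × 0.60 = 102 DEs. The sample size reproduces and is not at issue.

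**2. Can the combined index look good with an uninformative device?** Simulation at participant level, with assumed coefficients: 1000 trials of 200 patients, 160 for training and 40 for testing, ridge logistic model, about 60% events, two informative clinical covariates (log-odds 0.8 and 0.5 per SD) and five pure-noise MouthLab features.

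| Model | Mean test AUC |
|---|---|
| Combined | 0.70 |
| Clinical only | 0.72 |
| MouthLab only | 0.50 |

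The combined index exceeded an AUC of 0.60 in 88% of trials. Only the second and third rows reveal that the device contributed nothing, and the article plans neither.

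**3. How hard is the stated target (sensitivity above 80%, PPV above 70%)?** With prevalence p, PPV = 0.8p/(0.8p + FPR(1 − p)). Setting PPV to 0.70 gives FPR = 0.8p × (0.3/0.7)/(1 − p). In an equal-variance binormal model, AUC = Φ((z(0.8) − z(FPR))/√2).

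- Participant level, p = 0.60: FPR = (0.48/0.7 − 0.48)/0.4 = 0.514; AUC = Φ((0.842 − 0.036)/√2) = 0.716. Flagging everyone already gives PPV 60%.
- 30-day windows, assuming 6 per patient: p = 100/(168 × 6) = 0.099; FPR = 0.038; AUC = 0.968.
- Two-week windows, assuming 13 per patient: p = 100/(168 × 13) = 0.046; FPR = 0.016; AUC = 0.982.

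A clinical-only score with AUC 0.75, at sensitivity 80%, would have PPV 73% at participant level but only 16% (30-day) or 8% (two-week) at window level. Performance Evaluation classifies observation periods, so the 0.72 figure is a participant-level illustration only.

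**4. Could the missing comparison be estimated?** Assume AUC 0.70 without and 0.80 with MouthLab and a correlation of 0.5 to 0.7 between the two AUC estimates. Hanley-McNeil standard errors at participant level; SE of the difference = √(s₁² + s₂² − 2r·s₁·s₂).

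| Data used | Patients (DEs) | 95% CI half-width | Power |
|---|---|---|---|
| 20% hold-out | 34 to 40 (20 to 24) | 0.12 to 0.16 | 22% to 38% |
| Leave-one-patient-out | 168 to 200 (101 to 120) | 0.05 to 0.07 | 77% to 97% |

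These figures treat cross-validated predictions as one independent sample and do not model windows within patients, so they are a guide to order of size.

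**The case against.** **The objective is the combined index.** This stands. No superiority of MouthLab over clinical data is stated as a hypothesis, and the sentence in Expected Findings that names MouthLab says that its signals are used together with subjective and clinical data. The point therefore concerns what may be concluded about the device; it is not that a declared hypothesis goes untested.

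**Lead-time analysis already isolates the device.** This stands in part. Age and comorbidity hardly change between one patient's windows, so they cannot make predicted risk rise shortly before a DE, and Outcome Modeling does plan to study that time frame. But the monthly dyspnea and functional-status scores also vary and are not separated from MouthLab. The evidence is indirect and gives no size.

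**Clinical data alone could not reach the target.** At observation-period level this is probably right, since the required AUC is about 0.97 to 0.98 under the assumed window counts. A reader might infer from the participant-level 0.72 that age and comorbidity would suffice; the unit of evaluation in the plan does not support that. The inability to attribute or quantify remains at either level.

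**The article is condensed.** It lists a second modelling step without a first, and the full protocol or SAP may hold a benchmark. If so, stating it settles the point. The article does, however, set out inputs, comparison and metrics in some detail, and the comparison it names changes only the algorithm.

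**Conclusion.** The point holds in this form: under the analysis described, AIDI performance cannot be attributed to MouthLab and the device's added value is not quantified, while the rationale rests on its physiological signals. A reader might go further and infer that the trial cannot show that the device predicts anything. The documents do not support that: the data to be collected permit the comparison, and the lead-time analyses bear on it indirectly. This is a gap in the planned analysis and can be closed within the study.

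Its size depends on the unit of evaluation. At participant level a modest clinical score (AUC about 0.72) would meet the stated target without the device; at observation-period level that is unlikely. The clinical AUCs, the correlation, the windows per patient and the simulation coefficients are all assumptions. The absence of a benchmark without MouthLab depends on none of them. The change is recommended because it is cheap and bears directly on the conclusion that readers will draw.

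**What to change.** In Outcome Modeling and Performance Evaluation, for each τ, fit the same algorithm to:

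- (a) clinical and survey data only;
- (b) the full AIDI;
- (c) optionally, clinical and survey data plus the simple vital signs that MouthLab records (heart or pulse rate, oxygen saturation).

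Report the paired difference (b) − (a), and (b) − (c) if (c) is fitted, in discrimination and in sensitivity at a fixed specificity, at observation-period level with patient-clustered confidence intervals. Estimate them by leave-one-patient-out cross-validation. The article now holds this scheme as a fallback; for this comparison it should be planned from the start, and the 20% hold-out should not be relied on alone.

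Word any statement about MouthLab's contribution according to (b) − (a) and its interval, and any statement about the additional parameters according to (b) − (c). Where the difference is not reported, limit the conclusion to the combined index.

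The cost is analysis work only; no new patients or measurements are needed. The downside is that the increment may turn out small or imprecise, and a wide interval should not be read as showing that the device adds nothing.

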## Methods

### Study Design

This is a national, longitudinal, observational study. Potentially eligible patients will be identified using the US Department of Veteran Affairs (VA) Corporate Data Warehouse (CDW) and the COVID-19 Shared Data Resource. A total of 200 patients who have a history of “severe” COVID-19 infection in the previous 3-6 months and at least 1 of the specified comorbidities will be recruited. Severe COVID-19 is defined as requiring hospitalization for acute COVID-19 or its complications. Participants will be required to use the MouthLab device twice daily and to complete monthly surveys administered remotely either by phone or through a web portal. Data will be used to develop a machine learning–based algorithm to detect DEs among patients in the postacute COVID-19 phase.

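### The outcome window has no minimum gap after the last reading, and the >80% sensitivity and >70% PPV expectations are tied to no τ, lead or scoring unit, so last-day recognition counts as prediction

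*Protocol article*

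**What the plan says.** Outcome Modeling sets the outcome: "We will define the outcome as patients experiencing a DE within τ time units (DEτ"). The output is "a predicted probability of a DE occurring within the following τ days given observations of a fixed observation interval". The article names no primary τ: "For different values of τ, we will deploy a series of more sophisticated models".

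The features run up to the latest reading (Feature Engineering and Selection): "At each time t, we will include the most recent observations, changes since the last reading, trends". Study Design gives the frequency: "Participants will be required to use the MouthLab device twice daily".

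The Methods part of the abstract states the performance expectation: "the study expects the model to have a sensitivity of >80% and a positive predicted value of >70" (per cent). It also concedes how ease of prediction depends on time: "the closer to the event, the easier the prediction". The Introduction gives the purpose: "early prediction and real-time risk triaging using the AIDI may support better clinical decision-making, thus preventing complications".

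Performance Evaluation plans accuracy, false positives and false negatives for each τ, and lead-time statistics overall and in subgroups. For the leave-one-patient-out option it scores each observation period. It does not state the unit for the 80:20 test set or for the final detection performance.

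**The concern.** The window has an upper limit, τ, but no lower one. A reading a few hours before a DE is labelled positive in the same way as a reading a week before. These late readings are the ones the article itself calls easiest, and they are of least use for its stated purpose of warning early enough to prevent complications.

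Varying τ does not separate them. A DE within 14 days includes a DE within 1 day, so the late readings sit inside the positive class at every τ. A headline sensitivity or PPV computed under this rule mixes recognition of an illness already under way with advance warning, and the reader cannot tell the shares apart.

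The calendar date adds to this. DEs are gathered after data collection from warehouse entries, outside records and surveys, and they include new diagnoses and treatment changes. If many carry a date but no time (assumption), a reading on the DE date may come after care was sought and still be scored as prediction.

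**Working it through.** **The plan's own figures.** The >80% and >70% expectations have no derivation to reproduce. The sample-size figures do reproduce: 100/0.60 gives 167 completers (168 stated), and 168/0.85 gives 198 recruits (200 stated). They do not bear on this point.

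**Inputs from the article.** Two readings per day; window of τ days; 168 completers; 100 DEs; 6 months of monitoring, taken here as 180 days.

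**Assumed inputs, for illustration only.** Last-day detection p0; earlier detection pe per event, or e per reading; full adherence. Last day means the last 24 hours before the DE.

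**1. Share of positive readings on the last day.** 2/(2τ) = 1/τ. The share is the same at any fixed number of readings per day.

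| τ (days) | 1 | 2 | 3 | 7 | 14 |
|---|---|---|---|---|---|
| Last-day share | 100% | 50% | 33% | 14% | 7% |

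**2. A DE counts as detected by any alarm in its window.** Sensitivity without a gap = 1 − (1 − p0)(1 − pe). With a required lead of at least one day it is pe. At p0 = 0.85:

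| pe | No gap | One-day gap |
|---|---|---|
| 0 | 85% | 0% |
| 0.20 | 1 − 0.15 × 0.80 = 88% | 20% |
| 0.40 | 1 − 0.15 × 0.60 = 91% | 40% |

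A second illustration: last-day detection of 80%, and 1% of all other readings flagged at random. Sensitivity = 1 − 0.2 × 0.99^(2τ−2), which is 81%, 82% and 85% at τ = 3, 7 and 14. With a 24-hour gap it is 1 − 0.99^(2τ−2), which is 4%, 11% and 23%.

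**3. Each observation period is scored.** Sensitivity = p0/τ + e(1 − 1/τ). With e = 0 it cannot exceed 1/τ, so it cannot pass 50% once τ is 2 days or more. For the second illustration it is (2 × 0.8 + (2τ−2) × 0.01)/(2τ), which is 27%, 12% and 7%. Inflation remains: the excess over the with-gap value e is (p0 − e)/τ. With p0 = 0.85 and e = 0.20 this is 0.65/τ, or 22, 9 and 5 percentage points at τ = 3, 7 and 14.

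**4. The paired PPV expectation, at reading level.** Total readings are 168 × 180 × 2 = 60,480. In the second illustration, 1% random flags give about 605 alarms, against 100 × 2 × 0.8 = 160 last-day alarms. Simple PPV is 160/765 = 21%. If follow-up ended at the DE, taken at mid-study, readings fall to 68 × 360 + 100 × 180 = 42,480 and random flags to about 425. Counting the 26 flags that fall inside 14-day windows as correct (100 × 26 × 0.01), PPV is 186/585 = 32%. That index fails >70% either way. A cleaner last-day index could pass: at p0 = 0.85 there are 170 correct alarms, and PPV above 70% allows fewer than 170 × 0.3/0.7 = 72.9 false ones, that is 72 in about 60,000 readings (0.12%).

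**The case against.** The strongest reply is that the consequence depends on a scoring unit the article does not fix. The only unit it describes is the observation period, and there last-day alarms fall far short of 80% unless τ is 1 day. This stands. A reader might infer that the 80% expectation can be met with no usable warning whatever the analysis, and the documents do not support that. Event-level scoring is still a fair reading, because Sample Size aims to miss no DE and Performance Evaluation speaks of detecting DEs.

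Second, the article plans lead-time statistics and results for each τ, so an index that fires only at the end would show short leads. A reader might infer that late alarms would stay hidden; that goes too far. But these statistics are descriptive and put no condition on the headline sensitivity or PPV. The non-overlapping pre-event segments in Outcome Modeling could help to locate the signal in time, but they are described for building the training data and do not alter the outcome definition.

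Third, the expectation is paired. An index with many stray alarms would fail on PPV, as step 4 shows. This limits the second illustration and leaves open a specific last-day index.

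Fourth, a reader might infer that the plan expressly counts same-day or post-event readings. It does not. The wording leaves open whether the reading's own calendar day belongs to the window, and it does not say how DEs are time-stamped. Nothing excludes such readings, so this remains an inference.

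Finally, a condensed article may leave index-time rules to a fuller document, and the 80% is an expectation with no pass or fail rule. That excuses missing detail. It does not settle the point, because the outcome rule is stated, and following it as written mixes the two kinds of success.

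**Conclusion.** The concern holds in limited form. As written, the outcome admits readings immediately before a DE at every τ, and the >80% and >70% expectations carry no τ, lead or scoring unit. Under any-alarm scoring, or at τ = 1 day, last-day alarms alone could meet the sensitivity expectation: in the illustrations, 81% to 91% without a gap against 0% to 40% with one. Under per-period scoring they cannot reach 80% once τ is 2 days or more, but they still raise sensitivity, by 22, 9 and 5 points at τ = 3, 7 and 14 in the example.

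These sizes rest on assumed detection rates and full adherence. Only the 1/τ share follows from the window itself, given evenly spaced readings. Post-event readings matter only if DEs are dated to the day. The planned lead-time statistics reduce the risk of misreading but do not remove it. The point is worth correcting before the model is evaluated; it does not invalidate the study.

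**What to change.** For the headline sensitivity and PPV:

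- Count a DE only from the next calendar day, or from another prespecified minimum gap, up to τ days after the reading. The calendar-day rule works with date-only records, although an evening reading may then lead a DE by only some hours. A 24-hour gap needs event times and leaves nothing to score at τ = 1 day.
- Leave readings on the DE date out of the positive class, and out of the negative class too, so that they do not become false positives.
- State the τ and the scoring unit (event or observation period) to which >80% and >70% apply.
- Report the same-day figure separately, and detection by disjoint lead bands, for example 1–3, 4–7 and 8–14 days. The gap and bands are for the sponsor to choose and justify; the article gives no basis for particular values.

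The cost is a few lines in the outcome definition, plus relabelling and re-tabulating data already being collected. The downside is that headline sensitivity will be lower and rapid-onset DEs will count as missed.
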